# Effect of Live Environmental Music Therapy and Prerecorded Music on State Anxiety, Stress, Pain, and Well-Being Levels of Patients and Caregivers in the Emergency Department Waiting Room: Protocol for a Multicenter Randomized Clinical Trial

**DOI:** 10.2196/69131

**Published:** 2025-06-18

**Keywords:** anxiety, emergency department, mental health, music therapy, pain, stress, waiting area

## Abstract

**Background:**

Patients and caregivers attending emergency units often experience elevated levels of stress and anxiety. Music has been used in waiting rooms to reduce stress and anxiety, but existing studies on music therapy in emergency unit waiting areas are scarce and have limitations such as low statistical power and limited music selection.

**Objective:**

The aim of this study is to determine the effect of live Environmental Music Therapy and prerecorded music on state anxiety, stress, pain, and well-being levels in patients and caregivers in the emergency unit waiting areas of 2 hospitals in Colombia.

**Methods:**

This study is a multicenter randomized clinical trial, with 3 arms: standard care + live Environmental Music Therapy, standard care + prerecorded music, and standard care only. The primary outcome measure is the 6-item State-Trait Anxiety Inventory (STAI-6). Secondary outcome measures are pain and stress levels, both measured with Visual Analogue Scales (VAS), and well-being, measured with the Well-Being Numerical Rating Scales (WB-NRSs). The scales will be applied before and after each intervention. A total of 246 patients (82 in each arm) and 147 caregivers (49 in each arm) will be randomized.

**Results:**

Data collection for this study started on September 3, 2024, and as of the submission of the study (November 2024), 216 patients and 134 caregivers have been enrolled. It is expected that the results will be available by May 2025.

**Conclusions:**

This study seeks to contribute to improving the mental health, well-being, and quality of care of patients and caregivers in the waiting area of the emergency units. This is the first study in Colombia investigating the effect of live music therapy and prerecorded music interventions in the emergency department.

**Trial Registration:**

ClinicalTrials.gov NCT06510153; https://clinicaltrials.gov/study/NCT06510153

**International Registered Report Identifier (IRRID):**

DERR1-10.2196/69131

## Introduction

Emergency departments (ED) are critical for providing immediate care to patients with acute illnesses or those with medical emergencies. Its proper functioning depends on an organized triage system, which guarantees correct prioritization according to the urgency of pathologies [1]. Emergency health care professionals face a wide variety of medical needs and are exposed to complex social interactions with patients, family members, and caregivers. As a result, the environment in ED waiting rooms can be challenging and stressful for both patients and staff [2-5]. Distress may result from patients’ exposure to pain, injuries, discomfort, and possible diagnosis or medical treatments, which can increase their levels of anxiety and the feeling of uncertainty in the face of often prolonged waiting times [6]. Long waiting times in the ED have been shown to negatively affect patient recovery and patients’ and caregivers’ perception of the care quality provided [7-9]. In addition, patients can also experience nausea, hunger, or thirst, which, as they are not as easily detected by the staff as pain or dyspnea for example, can increase anxiety, insecurity, and discomfort in the waiting area [10]. Thus, it is important to consider environmental factors of ED waiting rooms, such as the quality of chairs, lighting, screens, and sounds, as they also affect the emotional states of patients and caregivers [11].

To mitigate some of these challenges, music therapy and other music-based interventions are increasingly applied in EDs. Early publications include reports of nursing teams using music in the pediatric emergency ward to reduce behaviors such as crying and screaming in children [12,13]. More recent studies highlight the benefits of prerecorded music in reducing anxiety [14-16] or pain [17] levels in adult patients in ED observation rooms. A study on live music therapy in emergency rooms was conducted by Mandel et al [18], including 180 patients (90 intervention, 90 control) who received music therapy sessions over a 3-year period. Although no statistically significant differences were found in patient satisfaction, stress, and pain levels decreased significantly in those patients who received music therapy. Furthermore, staff reported that music therapy favored the overall care experience and patients expressed a desire to have music therapy intervention in the ED again [18].

With respect to waiting rooms, recent literature reviews confirm the potential benefits of music in these settings but also highlight the methodological heterogeneity of studies, small sample sizes, limited descriptions of the music used, and a lack of live music approaches [19,20]. One of the few studies reporting live approaches was conducted by Van Dokkum et al [21] and Rossetti et al [22]. Van Dokkum et al [21] investigated the impact of visiting artists performing live music in waiting rooms at a hospital in New York, showing a positive impact on the sound environment. In a randomized controlled trial, Rossetti et al [22] investigated the effect of live Environmental Music Therapy (EMT) on anxiety levels and waiting time perception of patients and caregivers in the radiation therapy waiting room. The results showed a significant reduction in stress and anxiety levels in both patients and caregivers, in addition to shortening the perception of waiting time.

This study protocol seeks to expand the current knowledge on the use of music in ED waiting rooms by determining the effect of standard care + live EMT versus standard care + prerecorded music versus standard care alone on state anxiety, stress, pain, and well-being levels of in adult patients and caregivers in the emergency waiting rooms of the hospitals Clínica Keralty Ibagué and Clínica Iberoamérica in Colombia, South America.

## Methods

### Study Design

This study follows the SPIRIT (Standard Protocol Items: Recommendations for Interventional Trials) guidelines (Multimedia Appendix 1) for reporting randomized clinical trial (RCT) protocols [23] and is a multicenter, pragmatic, RCT with 3 parallel arms [24]:

Intervention group 1: Standard care + EMTIntervention group 2: Standard care + prerecorded musicControl group: Standard care alone

This study will be carried out in the emergency waiting room areas of the Clínica Keralty Ibagué and Clínica Iberoamérica within a 6-month period. The anticipated recruitment start date is September 2024.

### Study Participants and Setting

The study participants are adult patients and caregivers in the emergency waiting rooms of both hospitals. Both EDs are located in different cities in the country but belong to the same health care provider, which ensures similar standard care procedures for patients and caregivers. Both EDs serve subsidized, contributory, and prepaid health care users and both hospitals use the ESI (Emergency Severity Index) system for effective triage of patients. The ED waiting area at the Clínica Keralty Ibagué has 40 seats and the one at the Clínica Iberoamérica has 38 seats. Estimated wait times according to triage classification are as follows: triage 1: immediate attention (reanimation); triage 2: approximately 30 minutes; triage 3: approximately 1 hour; and triage 4 and 5: up to 6 hours. The 3 most common reasons for admission to the ED are (1) abdominal and pelvic pain, (2) fever of unknown origin, and (3) intestinal infections due to viruses and other pathogens.

#### Inclusion Criteria

The inclusion criteria are patients and caregivers of legal age present in the ED waiting rooms during the intervention and control conditions; patients whose triage does not represent an immediate threat to life or severely ill patients (ie, triage 3, 4, and 5); and patients and caregivers with the necessary literacy and cognitive skills to understand and fill out the questionnaires.

#### Exclusion Criteria

The exclusion criteria are patients and caregivers who do not consent to participate in the study; and patients and caregivers who report having hearing problems.

#### Sample Size

The sample size was calculated based on the primary outcome of this study using G*Power 3.1.9.7 (Heinrich Heine University Düsseldorf) [25] and considering that the study design corresponds to a 3×2 factorial design (3 groups and 2 repeated measures). Therefore, we will determine the effect of treatment between the groups using a 2-way ANOVA and repeated measures. We chose a statistical power of .80, a significance level of .05, and an effect size of =.01, the effect size was determined based on previous research [22] and the expected magnitude of differences between groups. The sample size calculation resulted in 246 participating patients, distributed in 82 per group.

In addition, a separate sample size calculation was performed for participating caregivers, following the same procedure as described for the patients and considering an effect size of η^2^=.017, resulting in 147 caregivers (49 per group). Both sample sizes are within the range reported in previous studies [22].

#### Participant Selection and Randomization

Selection of the participants will be made by convenience sampling. The intervention and control conditions will take place on the same day of the week (Tuesdays, Thursdays, and Fridays) and at the same hour (11 to 11:30 AM) at both hospitals. The order of the 3 conditions (EMT, prerecorded, control) will be randomized by days of intervention. For this, a block size randomization of multiples of 3 will be used, ensuring an equal number of interventions for each arm of the study. Intervention A will be established as EMT, intervention B as prerecorded music, and intervention C as standard care.

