#### Concealment

The concealment of the random assignment will be guaranteed using sealed, sequentially numbered, and opaque envelopes. The envelopes will be sealed with tamper-proof security tape and opened sequentially on each day of intervention. The envelopes will be kept in a folder that will be kept on a locked shelf inside each clinic, which will be in custody by the research assistant at each participating clinic. The envelope will be opened 10 minutes before the start of the intervention to give the music therapists time to organize their equipment and instruments.

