### Data Analysis

Regarding the sociodemographic and medical data, a descriptive analysis will be carried out. For continuous variables and according to the nature of the data, measures of central tendency and interquartile range or mean and SD will be used, and evaluated with the Shapiro-Wilk test. Categorical variables will be analyzed and summarized using frequencies. Association tests of categorical variables will be evaluated using the chi-square statistic or Fisher exact test in the case of tables with cells with expected values less than 5. For the comparison of measures of central tendency in the cases of quantitative variables, tests such as the Student *t* test or sum of Wilcoxon or Kruskal–Wallis ranges will be performed, depending on the presence or not of normality in the distribution of the variables. A statistical significance value of 5% will be used for all hypothesis test cases.

The analysis regarding the effect of the interventions will be carried out separately by type of participant (patient or caregiver). The effect on state anxiety, stress, pain (only patients), and well-being will be evaluated using 3×2 factorial ANOVA. Then a post hoc analysis will be performed using the Student *t* test and Bonferroni adjustment. A multiple linear regression analysis will be carried out to evaluate the variables (state anxiety, age, sex, type of participant, waiting time, and reason for consultation) that modify the effect of the interventions on the state anxiety, stress, pain, and well-being levels. Only data from patients and caregivers who will complete both baseline and postintervention questionnaires will be analyzed. However, to avoid bias we will assess if the distribution of participants who did not fill out the postintervention questionnaires is similar among the groups.

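### Conditions are randomised by day, but the planned ANOVA and t tests treat participants as independent; if change scores correlate within a session, the 5% tests are too liberal and power falls below 0.80

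*Protocol article*

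**What the plan says.** **Allocation.** Participant Selection and Randomization makes the day the unit: "The order of the 3 conditions (EMT, prerecorded, control) will be randomized by days of intervention". Balance is also set at that level: "a block size randomization of multiples of 3 will be used, ensuring an equal number of interventions for each arm of the study". Under Concealment, the envelopes are "opened sequentially on each day of intervention". Sessions fall on "the same day of the week (Tuesdays, Thursdays, and Fridays) and at the same hour (11 to 11:30 AM) at both hospitals". Anticipated Findings lists the randomisation of intervention days among the design's strengths.

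**Analysis.** Data Analysis, run separately for patients and caregivers, states: "The effect on state anxiety, stress, pain (only patients), and well-being will be evaluated using 3×2 factorial ANOVA". It continues: "Then a post hoc analysis will be performed using the Student *t* test and Bonferroni adjustment". The supplementary regression considers "state anxiety, age, sex, type of participant, waiting time, and reason for consultation". Day, session and hospital are not in that list.

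**Sample size.** Sample Size uses G*Power for 3 groups and 2 repeated measures, power .80 and significance level .05. It gives 246 patients and 147 caregivers, with no ICC, design effect or number of days.

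**Abstract.** The Methods paragraph says: "A total of 246 patients (82 in each arm) and 147 caregivers (49 in each arm) will be randomized".

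**The concern.** Music, or its absence, fills the whole waiting room, so no individual is allocated separately. People in one session share the performance, the room and whatever happens there during those 20 minutes. The live music is meant to adapt to the room (Intervention Protocol), so live sessions differ from one another by design. Potential Limitations adds that sound levels were not formally measured.

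A participant-level ANOVA takes its error term from variation between people and assumes that they are independent. The repeated factor handles correlation within a person, not between people in the same session. Bonferroni handles the number of comparisons. Neither repairs the mismatch, and Potential Limitations does not mention it. At stake are the error rate of the primary STAI-6 test, that of every secondary test, and the stated power.

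**Working it through.** **1. Reproduce the plan's figures.** The test is taken as the group×time interaction: λ = f²·N·2/(1−ρ), df = (2, N−3). Two assumptions are needed: ρ = 0.5, which is not stated, and the patient effect size of .01 read as η² (its symbol is lost in the text), so f ≈ 0.10. For caregivers η² = .017, so f ≈ 0.13.

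- Patients: λ = 0.01·246·4 = 9.84; power 0.804.
- Caregivers: λ = 0.0169·147·4 = 9.94; power 0.804.

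These are the smallest multiples of 3 that reach 0.80, so both stated sizes are matched by a calculation for independent individuals with no clustering allowance.

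**2. Number of sessions.** Results gives a start on 3 September 2024, with 216 patients and 134 caregivers enrolled by November. Tuesday, Thursday and Friday dates up to 1, 15 and 30 November number 27, 33 and 39. Two hospitals double this to at most 54–78 sessions.

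- Patients per session: at least 216/78 = 2.8 to 216/54 = 4.0.
- Caregivers per session: at least 134/78 = 1.7 to 134/54 = 2.5.
- If both hospitals share one condition per date: 216/39 = 5.5 to 216/27 = 8.0 patients per cluster.

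**3. Type I error of the planned F test.** With two time points, the interaction test is equivalent to a one-way F test on change scores, so the relevant ICC is that of the change score. Assume 60 sessions (20 per arm) with people falling into them at random. With n people and K sessions per arm, a participant shares a session with (n−1)/K others on average. Then, approximately:

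DE = 1 + [(n−1)/K]·ICC, and type I error ≈ P(F(2, N−3) > c/DE), where c is the nominal 5% critical value.

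- Patients: (82−1)/20 = 4.05; c = 3.033 on (2, 243) df.
- Caregivers: (49−1)/20 = 2.40; c = 3.059 on (2, 144) df.

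| ICC (assumed) | DE, patients | Type I, patients | DE, caregivers | Type I, caregivers |
|---|---|---|---|---|
| 0 | 1.00 | 5.0% | 1.00 | 5.0% |
| 0.01 | 1.04 | 5.6% | 1.02 | 5.4% |
| 0.05 | 1.20 | 8.2% | 1.12 | 6.9% |
| 0.10 | 1.41 | 11.8% | 1.24 | 8.8% |
| 0.20 | 1.81 | 18.9% | 1.48 | 13.0% |

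Simulation with unequal session sizes agrees. At ICC 0.05, 0.10 and 0.20 it gives 8.1%, 11.9% and 18.7% for patients and 6.7%, 9.0% and 13.5% for caregivers; patients at ICC 0.01 give 5.4–5.6%. With equal session sizes the patient figures are lower: 7.8%, 10.3% and 15.5% at ICC 0.05, 0.10 and 0.20. With 8 patients per cluster of equal size, as under a shared sequence, they are 6.2%, 11.1% and 17.8% at ICC 0.01, 0.05 and 0.10.

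**4. Power of a valid analysis at N = 246.** With m patients per cluster and unrounded f² = .01/.99, λ = 4·f²·246/DE = 9.94/DE, where DE = 1 + (m−1)·ICC and the denominator df is 246/m − 3.

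| m | ICC | DE | Power |
|---|---|---|---|
| 3 | 0.01 | 1.02 | 0.79 |
| 4 | 0.05 | 1.15 | 0.73 |
| 4 | 0.10 | 1.30 | 0.67 |
| 8 | 0.05 | 1.35 | 0.63 |
| 8 | 0.10 | 1.70 | 0.52 |

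**The case against.** The strongest reply is that the harm is conditional and may be small. The planned test looks at change over about 20 minutes, so anything about a day that moves the before and after scores equally cancels out. Only session effects on the change remain, and no passage indicates how strong they are. At ICC 0.01 the error rate is hardly above 5%. With 78 sessions and ICC 0.05 it is about 6.5–7.3% for patients. This stands, and it limits what can be claimed.

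A reader might go further and infer that the p-values are certainly too small, or that a significant music effect would merely show which days were quiet. The document supports neither. The first needs an ICC above 0, which is not given. The second describes a comparison of after-scores rather than of change. Very large error rates, obtained by assuming far fewer sessions, are not supported either: the enrolment dates give an upper limit on sessions but no lower one.

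The Abstract's statement that participants will be randomised is loose wording. The Methods section states day randomisation openly, so that is a reporting point. The document also plans no confidence intervals; any that are too narrow would follow from the same standard errors.

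The mismatch itself is untouched. The article names the tests, so this is not a detail left to an analysis plan, and those tests do not follow the allocation it describes. An unknown ICC is a reason to model session, not to assume zero.

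**Conclusion.** The concern holds in conditional form. Days are randomised, participants are analysed and powered as if independent, and nothing else in the document corrects this. If the session-level ICC of the change score is above 0, the nominal 5% tests are too liberal. Under the 60-session assumption the error is about 5.5% to 19% for patients and 5% to 13% for caregivers over ICC 0.01 to 0.20. It is larger with fewer sessions, or if both hospitals share one sequence. The document does not settle the latter, although envelopes kept inside each clinic point towards separate sequences. Power at 246 patients falls from the stated 0.80 to about 0.79 in the mildest case considered and 0.52 in the worst. The direction rests on the text; the size rests on assumed ICCs and session counts. Because it affects the primary test and every secondary one, it must be fixed.

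**What to change.** Before the analyst is unblinded, replace the ANOVA and t tests, separately for patients and caregivers, with a linear mixed model of the post score:

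- fixed effects for arm, baseline score and hospital;
- a random intercept for session (hospital × date, or date alone if both hospitals share one sequence);
- Satterthwaite or Kenward-Roger degrees of freedom;
- Bonferroni-adjusted pairwise arm contrasts taken from the model.

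State in advance that session-level means will be analysed if the session variance cannot be estimated. This is a real possibility for caregivers, at roughly two per session. Describe the trial as randomised by day (cluster), say whether the hospitals share a sequence, report sessions per arm and the ICC, and restate power with clustering. If the analysis has already been run, report the change as a deviation.

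**Cost.** The change is to wording and model code, plus a session date and hospital for each record. A session-based schedule should supply these, although the article's list of collected data names neither. The real cost is power below the stated 0.80: slight at ICC 0.01, substantial at ICC 0.10 with larger clusters. Keeping the ANOVA does not recover that power. By design effect alone, with 4 per cluster and ICC 0.05, the target would be 246·1.15 ≈ 283 patients and 147·1.15 ≈ 170 caregivers.

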#### Blinding

Due to the nature of the interventions, music therapists, patients, caregivers, and data collectors, will not be blinded. Data analysis will be carried out by a member of the research team blinded to the result of the randomization.

#### Concealment

The concealment of the random assignment will be guaranteed using sealed, sequentially numbered, and opaque envelopes. The envelopes will be sealed with tamper-proof security tape and opened sequentially on each day of intervention. The envelopes will be kept in a folder that will be kept on a locked shelf inside each clinic, which will be in custody by the research assistant at each participating clinic. The envelope will be opened 10 minutes before the start of the intervention to give the music therapists time to organize their equipment and instruments.

#### Primary Outcome Measure

The primary outcome measure is state anxiety, measured with the Spanish version of the 6-item State-Trait Anxiety Inventory (STAI-6). In its original version, the STAI consists of 40 items, of which 20 measure trait anxiety and 20 items measure state anxiety [26]. The STAI-6 is a short version of the state scale and consists of 6 items evaluated on a 4-item Likert scale. The STAI-6 was validated in its original English version by Chlan et al [27], and its Spanish version by Perpiñá-Galvañ et al [28,29], and has been successfully used in a previous study on EMT in radiotherapy waiting rooms [22]. The STAI-6 will be applied before and after each intervention.

#### Secondary Outcome Measures

Stress: Stress levels will be measured by the Visual Analogue Stress Scale (VAS-S). The VAS-S consists of a 10-cm line divided into 10 points, each separated by 1 cm. 0 means the complete absence of stress, and 10 is the maximum possible stress. The VAS-S has been validated by Lesage et al [30] and was recently applied in a study on stress levels of caregivers or companions in the ED [31]. A cutoff of 7 points has been established as a significant stress level [32]. The VAS-S will apply before and after each intervention.Pain (patients only): Perceived pain levels by patients will be measured with the Visual Analogue Pain Scale (VAS-P) consisting of a line of 10 centimeters divided into 10 points, each separated by 1 centimeter. 0 means complete absence of pain and 10 the maximum possible pain. The VAS-P is widely used in research and minimum clinically important differences pre-post interventions range from 9 millimeters [33] to 14 millimeters [34]. The VAS-P scale for pain will be applied before and after each intervention.Well-being: Well-being will be measured by the Well-being Numerical Rating Scales (WB-NRSs) developed by Bonacchi et al [35]. The WB-NRSs consist of a line divided into numbers from 1 to 10. 1 indicates a state of absolute distress and 10 a state of absolute well-being. The WB-NRSs uses 5 scales to measure well-being in 5 dimensions: physical, psychological, spiritual, relational, and general. The WB-NRSs will be applied before and after each intervention.

